#### Randomization

Cluster randomization will be used with the cluster defined as barbers/barbershops, and all participants recruited and offered intervention by each barber randomized to the same group as the barber (either intervention or control group). Randomization at the level of individual youth will not be feasible owing to the danger of contamination.

### Allocation

A total of 40 clusters, each with 15 participants, is targeted. A total of 20 clusters will be randomly allocated to the DWM intervention group, while the other 20 clusters, with 15 members each, will be randomly assigned to the waiting list control (WLC) group. A simple randomisation approach will be used, either using randomization software or simple manual approaches.

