**Methods:** The project will be carried out in Bungoma and Kitale towns in Western Kenya, among youths (18-29 years) visiting selected barber shops for a routine haircut. The project will collaborate with local musicians to produce mental health-themed music to be played in selected barber shops. Selected barbers will be trained as facilitators in the delivery of doing what matters in times of stress (DWM). The barbers will use MH-themed music to initiate discussion on the project with youths visiting their barbershops. Those who consent will be screened for eligibility by research assistants, and eligible ones will be enrolled in the project by the barber. The barbers will help deliver the DWM intervention, which will last five weeks for each participant. Thereafter, selected participants will receive entrepreneurship and life skills training and support. A mixed-method approach involving a cluster randomized control trial design with each barber used as a cluster (40 clusters with 15 youths each); hence, a total of 600 youths (300 cases and 300 controls) and qualitative evaluation will be used for the evaluation. The 40 clusters will be randomised to either the intervention or control group using a randomisation ratio of 1:1. The project outcomes; depression, anxiety, stress, self-identified problems, resilience, functioning and mental health awareness will be assessed at baseline and post-intervention.

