### Target population

The study will target youths aged 18 to 29 years living in urban areas of Kitale town of Trans-Nzoia county and Bungoma town in Bungoma county. The age group of 18-29 years was selected based on the scarcity of data regarding interventions targeting this age group in the targeted settings.

A total of 40 barbershops and barbers will be included in the study (20 barbershops per county). The barbershops will be invited to participate. The barbers/barbershops will act as the study clusters.

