### Sample size

The target sample size for this study will be 40 barbers/barbershops (clusters) with 15 youths from each, translating to 600 youths (300 youths in the intervention group and 300 youths in the control group). The cluster-randomised trial sample calculator based on the National Institutes of Health will be used (<https://researchmethodsresources.nih.gov/>). The sample size will be determined with the ability to detect as low as Cohens d of 0.40, while taking into account an attrition rate of 20%. A statistical power of 0.8 and two-tailed alpha of 0.05 with a correlation coefficient of 0.5 between baseline and endpoint scores will be assumed. An interclass correlation of 0.02 will be assumed to allow for possible clustering effects.

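### Shops are allocated without restriction by town and town is not prespecified in the model: a modest loss of precision that can be avoided at almost no cost

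*Protocol*

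**What the plan says.** - **Number of shops and their spread** (Protocol, Target population): "A total of 40 barbershops and barbers will be included in the study (20 barbershops per county". The two counties are represented by one town each, Kitale and Bungoma.
- **Ratio and split** (Protocol, Abstract and Allocation): "The 40 clusters will be randomised to either the intervention or control group using a randomisation ratio of 1:1", and "A total of 20 clusters will be randomly allocated to the DWM intervention group". The remaining 20 go to the waiting list.
- **Method** (Protocol, Allocation): "A simple randomisation approach will be used, either using randomization software or simple manual approaches". Neither this section nor the Randomization section mentions stratification, blocking, matching or any other restriction by town.
- **Analysis** (Protocol, Data analysis): a linear mixed model adjusts for the baseline outcome score and for those sociodemographic variables that differ significantly between the arms at baseline. Categorical variables are compared by χ² test. Town is not named as a covariate. Area of residence is recorded at baseline (Quantitative data collection), but its coding is not given.

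**The concern.** Town is the one structural factor known for every shop before randomisation, and the design already fixes it at 20 shops each. The allocation does not use that information. With only 40 units, a chance imbalance between towns is likely. If the towns differ in distress, economy or services, part of that difference moves with the arm contrast in the trial that is actually run.

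The analysis does not settle the matter in advance. Whether this design factor enters the model depends on a test of observed imbalance that treats 600 clustered youths as independent.

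There is also a question of wording. Simple randomisation, read strictly, assigns each shop independently and so does not guarantee the 20:20 split given in the same section.

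**Working it through.** **Inputs from the protocol.** 40 shops, 20 per town, 20 per arm; "40 barbers/barbershops (clusters) with 15 youths from each, translating to 600 youths"; "ability to detect as low as Cohens d of 0.40"; "A statistical power of 0.8 and two-tailed alpha of 0.05"; "correlation coefficient of 0.5 between baseline and endpoint scores"; ICC 0.02; attrition 20%, so 15 × 0.8 = 12 completers per shop. **Assumed, not in the protocol:** a town difference δ of 0.2–0.3 SD.

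**1. The plan's own size.** 40 × 15 = 600 is consistent as a count. The stated inputs need fewer youths. Without baseline adjustment, 99 per arm × design effect 1.28 = 127, and 127/0.8 = 159 per arm, or 318 in total. With variance factor 1 − 0.5² = 0.75, 74 × 1.28 = 95, and 95/0.8 = 119 per arm, or 238 in total. The trial therefore has power to spare, which limits the harm below.

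**2. Strict simple randomisation, Binomial(40, 0.5).** P(20:20) = 12.5%; P(24:16 or worse) = 26.8%. The power cost is trivial: at 24:16 the relative efficiency is 4 × 24 × 16/1600 = 0.96, and power at d = 0.40 without baseline adjustment is 0.973 against 0.978.

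**3. 20 of 40 drawn without strata, Hypergeometric(40, 20, 20).** Let k be the number of intervention shops in one town.

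| Split within a town | Probability |
|---|---|
| 10:10 | 24.8% |
| 12:8 or worse | 34.3% |
| 13:7 or worse | 11.3% |
| 14:6 or worse | 2.6% |

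**4. Shift in one realised contrast with town omitted and before baseline adjustment.** Shift = δ × (2k − 20)/20. For δ = 0.3 it is 0.3 × 0.2 = 0.06 SD at 12:8 and 0.3 × 0.3 = 0.09 SD at 13:7. Over all draws the shift averages zero.

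**5. Effect on the standard error with town omitted.** The baseline-adjusted SE with 12 completers per shop is √(0.75 × 2 × 1.22/240) = 0.0873, where 1.22 = 1 + 11 × 0.02 and 240 = 20 × 12. Var(k) = 20 × 0.25 × 20/39 = 2.564, so the shift has variance δ² × 2.564/100 = 0.02564 δ².

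- No part of δ removed by baseline adjustment: for δ = 0.2, √(0.007625 + 0.001026)/0.0873 = 1.065; for δ = 0.3, √(0.007625 + 0.002308)/0.0873 = 1.141.
- Half of δ remaining, as expected if the town difference is the same at baseline and endline and the adjustment slope is 0.5: for 0.10, √(0.007625 + 0.000256)/0.0873 = 1.017; for 0.15, √(0.007625 + 0.000577)/0.0873 = 1.037.

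The SE increase is thus about 2–4% in the second case and 7–14% in the first.

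**6. Would the baseline test select town?** If area of residence is coded as town, an 11:9 split gives 165/300 against 135/300. Then χ² = 600 × (165² − 135²)²/300⁴ = 6.0, p = 0.014. At 12:8, χ² = 24.

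**7. Cost of stratifying and fitting town.** Between-cluster degrees of freedom go from 38 to 37. Power at d = 0.40 goes from 0.9716 to 0.9714 without baseline adjustment and stays at 0.9938 with it.

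**The case against.** **The 20:20 split.** A reader might infer that the trial will usually miss its planned split, since independent assignment gives 20:20 only one time in eight. The text does not support this. The Allocation section speaks of 20 clusters and the other 20, which reads naturally as drawing 20 of 40, with simple meaning unstratified. This part is mainly wording, and even a 24:16 split would cost almost no power.

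**Bias.** A reader might call the 0.06–0.09 SD shift a bias. It is not one in expectation: it describes a particular unlucky draw before adjustment, and a model with shop as a random effect already counts between-shop variation in its interval.

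**The existing covariate rule.** If area of residence identifies town, the χ² rule brings town into the model at 11:9 or worse at the planned size, and the shift is then adjusted for. This is the strongest objection, and it stands on that condition. It does not dispose of the point: the coding is not stated, finer coding might not bring town in, and a design factor should not depend on a test that ignores clustering.

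**The upper SE figures.** The 14% figure is generous. A 0.3 SD difference between two equal towns is a variance of 0.3²/4 = 0.0225, above the whole assumed ICC of 0.02. If that ICC spans all 40 shops, the largest compatible difference is 2 × √0.02 = 0.28 SD. Even with a 14% larger SE, power at d = 0.40 would fall only from 0.996 to 0.980.

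**Tampering.** A reader might infer from the manual option that the allocation is open to manipulation. The protocol does not say who draws or how, and drawing lots is a legitimate method. Nothing in the text supports that charge.

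**Conclusion.** The point holds as a modest, avoidable weakness. The protocol neither balances the arms within town nor prespecifies town in the model. Three draws in four leave the towns unequally split, and about one in three leaves a split of 12:8 or worse.

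The consequence is some lost precision and face validity, and only if town stays out of the model. The 2–4% increase in SE assumes a town difference of 0.2–0.3 SD with half remaining after baseline adjustment; 7–14% is the upper end if none is removed. The probabilities are firm; the SE figures depend on a town difference the protocol does not give. The trial's ability to detect d = 0.40 is not threatened. This rests on the protocol alone: if a SAP already lists town as a covariate, only the allocation sentence needs attention.

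**What to change.** In Allocation, replace the sentence on method with: within each town, 10 shops are randomly allocated to DWM and 10 to the waiting list from a computer-generated list. This guarantees 20:20 overall and 10:10 in each town, and it removes the ambiguity of the word simple. In Data analysis, name town as a prespecified fixed effect in the mixed model, whatever the baseline comparisons show.

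The cost is two sentences and one between-cluster degree of freedom. The sample size stays at 600.

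If allocation has already taken place, which is possible since the study timeline runs to November 2024, prespecify town in the model before the analysis and report the method actually used and the town-by-arm split. Most of the benefit is kept: with town fitted, a 12:8 split raises the SE by a factor of 1/√(1 − 0.2²) = 1.02 relative to 10:10.

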### Blinding

Single blinding will be applied with only the data collectors/outcome assessors and the biostatistician analysing the data blinded of the participant's/barbers group allocation. Due to the nature of the intervention, it is not possible to blind participants and the barbers delivering the intervention.

### Intervention procedure

We will train the barbers on basic mental health information, helping skills and regarding the DWM intervention. We will use the trained barbers as helpers to deliver the DWM intervention. Doing What Matters in Times of Stress intervention booklets and audio developed by WHO (WHO, 2020) will be used by the trained barbers as intervention material.

The trained barbers will meet the participants in three meetings:

**Introductory Appointment:** this will cover an introduction to the stress management guide, a discussion of interest, assessment, and planning. This session will take up to one hour.

**One-week follow-up:** This will cover using the stress management guide and support with overcoming barriers or problems with use and clarifying concepts. This will take upto 50 minutes.

**One-month follow-up:** This last session will cover the use of the DWM stress management guide, support overcoming barriers or problems with use, planning for continued future use, and completing follow-up assessment and goodbye or referral. This will also take approximately one hour. After the meetings, the youths in the intervention will be expected to engage with the provided intervention audio and illustration guides on their own. In case of any difficulties, they will be free to contact and engage the trained barbers to explanation and help in understanding the content. The intervention supported by the barber will last for five weeks for each participant, after which the Research

Assistants will conduct a post-intervention assessment. The intervention will be delivered in English.

The project will run a small validation exercise to verify understanding and develop a catalogue for words used in the local vernacular language that may not be well understood if spoken in English. The barbers will be trained always to ensure the participants understand the content. A word catalogue will be written to help each barber use the correct idioms based on the vernacular of the participants.

#### Entrepreneurship and life skills intervention component

A small sample of the youths (100) will be included in this component. These participants will be randomly selected from participants in the DWM intervention (50) and waiting list control (50) group participants. Selection will be based on having reported economic hardship or unemployment as the main problem faced during pre-assessment with the PSYCHLOPS tool. The selected youth will be invited for two-day entrepreneurship and life skills training.

After training, the youths will be asked to come up with business ideas in the area of interest they would like to pursue related to their area of skills. They will then be paired in groups based on similar interests and given interest-free micro-loans to start small businesses. They will also receive personalised mentorship from experienced entrepreneurship and apprenticeship experts. Those offered micro-loans will be required to keep records of their expenditure and income. They will be required to repay the loan in equal monthly instalments from the third month after the loan has been disbursed to them. Research assistant or project coordinator will follow up monthly with them and gather data on the performance of their businesses and income flow based on their records. The repaid amount will be loaned to other youths in a revolving manner.

As part of the intervention evaluation, in-depth qualitative interviews will be conducted to understand their views on the entrepreneurship component, including its usefulness, shortcomings, and aspects they would like improved.

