### Aims and objectives

Broadly, the project will seek to determine the feasibility and effectiveness of using local music and barber facilitated DWM to improve mental health outcomes and well-being in Western Kenya.

Specifically, the project will aim to test 1) the feasibility of using hip-hop and rap music to initiate a conversation on mental health among youths, 2) the effectiveness of the barber-delivered DWM intervention in improving mental health outcomes (depression, anxiety, stress, self-identified problems, functioning, and resilience) among participants 3) changes in knowledge, and attitude towards mental health among the youths involved in the intervention and 4) the impact of the entrepreneurship and life skills training on economic outcomes and wellbeing of the participants.

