## Methods and materials

### Study design

A mixed-method study approach will be used with both quantitative and qualitative study designs. For the quantitative part, the project will utilise a two-arm, cluster randomised control trial design with an intervention and waiting list control group, with two outcomes assessment points: preintervention and post-intervention, which will be done after the five-week intervention. The qualitative design will mainly be used for process evaluation to gather in-depth information regarding the role of music in the project, understand participants' knowledge and attitude towards mental health, and assess the participants' engagement and satisfaction with the project.

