#### Control group

A waiting list control group will be used. They will be assessed at baseline and endline (5 weeks from the date of baseline assessment). They will receive the intervention after the intervention is complete in the intervention group.

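### Aim 4 promises a tested impact of the entrepreneurship component, but the data the protocol collects can only describe those who receive it

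*Protocol*

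**What the plan says.** The protocol's Aims and objectives section lists four things the project will test. The fourth is "the impact of the entrepreneurship and life skills training on economic outcomes and wellbeing of the participants".

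The section on the entrepreneurship and life skills component sets its size at 100 and takes half from each arm: "These participants will be randomly selected from participants in the DWM intervention (50) and waiting list control (50) group participants". On eligibility it adds: "Selection will be based on having reported economic hardship or unemployment as the main problem faced during pre-assessment with the PSYCHLOPS tool". After the training, those offered micro-loans keep records of spending and income, and staff collect business and income data from those records each month. In-depth interviews ask for participants' views of the component. Repaid money is lent on to other youths.

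On order, the Abstract describes the five-week DWM period and then says: "Thereafter, selected participants will receive entrepreneurship and life skills training and support". Study design describes the trial as one "with two outcomes assessment points: preintervention and post-intervention, which will be done after the five-week intervention". For the waiting list, Control group says: "They will be assessed at baseline and endline (5 weeks from the date of baseline assessment"; this arm receives DWM later.

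The pre-test questionnaire under Quantitative data collection covers work status among its demographic items, but lists no income item. The section on outcomes and measures names no economic outcome.

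**The concern.** To test an impact, the trial needs outcomes measured after the training and something to compare them with: an untrained group, or at the least the same measure taken before. The protocol describes none of these for income, and no wellbeing or mental health scale after the training.

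At stake is what may be concluded on one of four stated aims. Trainees are chosen because they name economic hardship or unemployment as their main problem, so some improvement without any training is likely. Waiting-list trainees also receive DWM after their endline, so later change in them could come from either source. An impact claim built on recipients' records alone would have no support. A statistical analysis plan could not repair this, because what is missing is data collection and a comparator, which the protocol itself fixes.

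**Working it through.** The plan's figure of 100 is 50 + 50. The protocol derives it from no power or precision target, so there is nothing further to reproduce. The check is whether the planned data contain a contrast that speaks to the training.

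1. **Trained against untrained, among those followed after the training.** Trained: 50 + 50 = 100. Untrained: 0. No comparative estimate exists.

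2. **Contrast between the arms.** Taking 300 youths per arm (Sample size), the training rate is 50/300 = 16.7% in each. DWM against waiting list therefore carries no information on the training. Comparing the 50 DWM trainees with the 50 waiting-list trainees would address DWM, since both groups are trained.

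3. **Before against after, economic outcomes.** Before: work status, no income. After: income and business records that start with the loan. This gives a post-loan course, not a before-after comparison.

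4. **Before against after, wellbeing.** Two scale assessments are scheduled, at baseline and about five weeks. With the training placed after the DWM period, 0 of 2 fall after it.

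5. **What a comparator could deliver (illustrative).** The component draws at random among youths reporting hardship, so those eligible but not drawn could be followed. The number eligible is not stated, so the pool size is an assumption. With 100 trained and (pool − 100) untrained, 80% power and two-sided 5%, the detectable difference in SD units is (1.96 + 0.84) × √(1/100 + 1/(pool − 100)). With 20% loss in both groups, the rate the protocol assumes under Sample size, the group sizes are multiplied by 0.8.

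| Assumed pool | Trained / untrained | Full follow-up | After 20% loss | 20% loss, result |
|---|---|---|---|---|
| 150 | 100 / 50 | 2.8 × √0.0300 = 0.48 | 80 / 40 | 2.8 × √0.0375 = 0.54 |
| 200 | 100 / 100 | 2.8 × √0.0200 = 0.40 | 80 / 80 | 2.8 × √0.0250 = 0.44 |
| 300 | 100 / 200 | 2.8 × √0.0150 = 0.34 | 80 / 160 | 2.8 × √0.01875 = 0.38 |

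At a pool of 100 or fewer everyone eligible is trained and no comparator exists. The figures ignore clustering by barbershop and any correlation among youths who run a business together.

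**The case against.** The strongest reply is that the component is ancillary. It takes a small sample, is absent from the Abstract's objectives, and has no place among the primary or secondary outcomes, so the trial's main inference does not depend on it. The protocol also never proposes to test aim 4 by comparing DWM with waiting list, and drawing equal numbers from each arm keeps the component balanced. All of this stands. It limits the weight of the point but does not remove the mismatch between aim 4 and the data.

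Three stronger readings are tempting, and the protocol does not support them:

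- A reader might infer that aim 4 yields nothing. It does yield description: loan-period business performance and income flow, and interviews on usefulness and shortcomings.
- A reader might infer that the protocol already creates a randomised comparator and wastes it. That holds only if more than 50 eligible youths per arm report hardship, and the protocol does not give that number.
- A reader might take it as settled that both assessments precede the training. The order rests on the Abstract's wording, and the bars of the timeline table cannot be read in the text available. If some training did fall before week five, there would still be no contrast between arms and no comparator for economic outcomes.

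It is also fair to say that a controlled follow-up is a new study element. It would change when revolving loans reach other youths, so it can only be offered as an option.

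**Conclusion.** The point holds for causal and comparative claims. As written, the protocol cannot estimate the effect of the training on economic outcomes or wellbeing: no untrained youths are followed, no baseline income is listed, income records begin with the loan, and no scale appears to be scheduled after the training. Descriptive results remain available. The conclusion on wellbeing depends on the training following week five; the conclusion on economic outcomes does not. The detectable differences describe a possible extension and rest on assumed pool sizes; they do not measure a defect in the present plan. The main DWM comparison is not called into question.

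**What to change.** Reword aim 4 so that it sets out to describe the business performance, income flow and experiences of trainees, and drop the terms impact and wellbeing. This costs nothing and changes no procedure.

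If the sponsor wants an impact estimate, and more than 50 eligible youths per arm report economic hardship, the option is to:

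- make and record the random draw within each arm, from a list of all eligible youths;
- keep the eligible youths who were not drawn as the comparator;
- add an income item at pre-assessment;
- assess income, PHQ-9 and WHODAS in both groups in the same month after the training, before revolving loans reach the comparators.

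The cost is one added assessment of the whole pool. Under the assumed pools that means 50 to 200 undrawn youths (pool − 100) plus the 100 trainees, and loan recipients among the trainees are already due monthly contact. Revolving loans to undrawn youths would be delayed. If the assessment is by telephone, it departs from the face-to-face administration planned for the scales, so both groups should be assessed in the same way. The eligible number per arm should be counted before choosing this option, because precision depends on it.
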